### Data monitoring and auditing

According to the recommended guidelines for clinical research in Japan (https://www.mhlw.go.jp/topics/bukyoku/seisaku/kojin/dl/161228rinsyou.pdf) and the institution regulations, data monitoring by a third party is not applicable for the RCT proposed here, since we are not providing participants with any medications nor surgery [56].

### Risks and benefits to participants

Participants are unlikely to encounter any serious risks or burdens.

Participants will possibly experience fatigue and discomfort during the Stroop task and the fNIRS recording. The participant will be informed in advance that, should they feel any discomfort, the test can be interrupted at any time.

The interventions in IVR are not particularly difficult and should not cause the participants any pain since they just have to stay still. Possibly, participants may experience a sense of dizziness or nausea due to the IVR display; to avoid that, exclusion criteria mention that people who are very sensitive to motion sickness are excluded. If, for some reason, the participant experiences any discomfort, they will have been previously informed that they may immediately interrupt the training. Any adverse events will be formally reported.

In accordance with the regulations of the institution, the participants will be given a monetary reward based on the number of hours invested performing the experiment. Therefore, in case the participant decides to leave the ongoing experiment, he/she will not receive any reward (i.e. only participants who complete the entire experiment will be rewarded).

## Discussion

The background of this RCT protocol study starts with two assumptions, based on data presented in the literature: (1) HIE has acute beneficial consequences on executive functions and their neural basis [17, 67]; and (2) the movements of their own virtual body can generate measurable consequences on their real body, comparable to the ones when we actually move [33, 41].

Consequently, we hypothesized that the same HIE intervention performed by their own virtual body (and not by the real participants’ bodies) can have the same beneficial acute effects on executive functions.

In order to confirm our hypothesis, 30 healthy young adults will undergo a vHIE, where the virtual body exclusively (the real body is still sitting) will perform 8 min of training, alternating 30 s of running and 30 s of slow walking; the same vHIE will be performed in two intervention conditions: 1PP, the virtual body will be displayed with the real one, spatially replacing it, and so it will be considered as their own; in 3PP, the virtual body will be displayed 1.5 m away on the right side of the real one, and so it will simply be considered as someone else. During the vHIE, we will record the HR: we predict finding a fluctuating trend of the HR during the intervention in 1PP (and not in 3PP), coherent with the virtual movements, as if the individual is actually performing them. In addition, we will ask the participants to report verbally any subjective feelings during the intervention, predicting that increased sensations of SoBO and SoA in 1PP respect to 3PP will be found.

To test our main hypothesis about acute beneficial effects on executive functions, before and after the two vHIE intervention conditions, we will record the participants’ performance of the Stroop task; at the same time, we will record cortical hemodynamic changes over the PFC with the fNIRS. We predict finding better performance, in terms of reaction time and accuracy, in the Stroop task and higher activation of the neural correlated areas (i.e. PFC) after the vHIE in 1PP (and not after 3PP).

If we confirm our hypothesis, it means that virtual training performed only with the own virtual body can raise the same physical but especially cognitive and neural consequences of a “real” physical one.

These results would contribute on different levels: from a theoretical perspective, this study would be another proof that the illusion of ownership over the virtual body is extremely effective and can be manipulated in order to arise effects on different levels (perhaps motor and cognitive). The simple fact that it is possible to show some effects consequent to the virtual illusion, comparable to the real ones, means the virtual movements are as effective as the actual ones. Our idea is that the SoBO (here the main variable manipulated through the perspective) can drive other aspects, such as motor function, and those, in turn, can drive others, such as cognitive functions. Theoretical models of motor control should clearly state the body and the sense of body ownership as a variable that can significantly affect the resulted action [68, 69].

From a clinical perspective, these results will have interesting applications: as previously mentioned, the intervention presented here can be very useful for sedentary people or those suffering from cardiopathy to start physical activity in a totally safe and entertaining way, or combining cardio or power exercise, and the IVR training, maximizing the efficacy of both on somatic and cognitive terms. In more extreme situations, patients with motor disorders can perform the virtual training but with the same beneficial effects as physical training [70].

However, this study has some limitations. All participants have to repeat the Stroop task four times (before and after the two IVR sessions). This could have a learning effect, or an effect due to the repetition itself, as a negative consequence. To avoid this, we will randomize the order in which the intervention conditions will be administered, but it is still possible to have a repetition effect. Another potential limitation concerns the control conditions of the intervention: several previous studies using IVR exploit the 3PP as a control condition. In some cases, it seems to have a sort of effect, although the reported effect is smaller than the one of the experimental condition. Finally, a difference between the previous study with a similar design and the current one concerns the type of intervention: in Kujach et al. [17], the training consists of a cycling exercise, while in our study we decided on a running exercise in order to be as consistent as possible with other previous studies with similar IVR setup [33].

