### Purpose

In this study, we combined the efficacy of the HIE on cognitive functions [17] with the possibility of manipulating SoBO and SoA offered by IVR [33, 41]. Our goal is to demonstrate whether a virtual HIE-based intervention performed exclusively by the considered-as-own virtual body, while the real individuals’ body is totally still (hereinafter vHIE), has acute cognitive and somatic beneficial effects on the real body, comparable to the ones that arise after actual physical training. We will compare the behavioral performance (speed and accuracy) with the Stroop task during the recording of the brain activity of the PFC with fNIRS (as in [15]), before and after the vHIE, in two interventions where we manipulate the visual perspective (1PP vs 3PP), known to induce or disrupt the SoBO and SoA over the avatar.

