### Trial design

This study is a cross-over (within-subjects) RCT conducted at the Smart-Aging Research Center (Institute of Development, Aging and Cancer, Tohoku University), Sendai City, Miyagi Prefecture, Japan. All participants will perform both experimental and control conditions (in other words, all participants will act as their own controls). This study (version 1.0) was registered with the University Hospital Medical Information Network (UMIN) Clinical Trial Registry (UMIN000034255) on 1 October 2018.

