### Interventions

Participants will visit the laboratory (located in the Smart-Aging Research Center) for two sessions, one week apart, corresponding to the two intervention conditions. In both sessions, the participants sit comfortably on a stool with their feet firmly resting on the ground and their arms relaxed by their sides. They have to wear the Oculus visor (oculus.com), equipped with two lenses that show the virtual world. They will be instructed to keep their bodies still but they can move and rotate their head, to explore the virtual body and the environment. The virtual environment, as well as the virtual bodies and the animations, is modelled in 3D Studio Max 2015 and implemented in Unity3D: it represents an open space with a green floor (simulating a meadow) and a natural-looking illuminated sky, with a visible horizon. Participants will see a gender-matched life-sized humanoid virtual body.

The intervention will be performed in two conditions. The experimental intervention displays the virtual body in 1PP, where the virtual body substitutes and is spatially coincident with the real one; in other words, to observe the virtual body, the participant has to look towards him/herself. The control intervention consists of displaying the same virtual body in 3PP, where the virtual body is collocated approximately 1.5 m to the left of the real participant’s body; in other words, to observe the virtual body, the participant has to rotate his head and look towards his left side.

In both conditions (1PP and 3PP), the intervention starts with a familiarization phase of 4 min (hereinafter baseline) where the gender-matched virtual body is displayed but there is no animation yet (i.e. the virtual body in both 1PP or 3PP is standing still). This phase is necessary to induce the illusory sensation of ownership over the virtual body (in 1PP) or not to induce it (in 3PP) (see the “Measurements” section for the online questionnaire on SoBO and SoA) for the baseline recording of the HR (see the “Measurements” section) and to check for eventual sickness problems due to the virtual display.

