### Outcomes

#### Primary outcomes

Considering that the main goal of this study is to determine that vHIE intervention performed with the own virtual body (1PP) has a beneficial effect on cognitive executive functions, the primary outcome of this study is the Stroop task (i.e. the cognitive domain), specifically the two related measurements (RT primarily and ER secondarily). The Stroop task is considered the primary outcome here because it is widely known as a measure for executive brain functions [21, 55]. As a key effect of the Stroop task, we will consider the so-called “Stroop interference” as the (average of incongruent trials– average of neutral trials) contrast, which is assumed to represent Stroop interference, for both RT and ER in each condition (1PP and 3PP).

Specific timepoints (before and after the vHIE) will be considered, but the main comparison in order to find a significant effect of vHIE on cognitive functions will be 1PP versus 3PP.

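### The Purpose and Discussion claim effects comparable to real exercise, but the trial compares only two virtual viewing perspectives and has no real-exercise condition or margin

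*Protocol article*

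**What the plan says.** All references are to the protocol article.

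**Goal and conclusions.** The Purpose asks whether a virtual exercise session (vHIE) "has acute cognitive and somatic beneficial effects on the real body, comparable to the ones that arise after actual physical training". The Discussion gives the hypothesis that exercise performed by the virtual body "can have the same beneficial acute effects on executive functions" as real high-intensity exercise. It then says what confirmation would mean: "it means that virtual training performed only with the own virtual body can raise the same physical but especially cognitive and neural consequences", matching those after real exercise. Further on it says that showing such effects "means the virtual movements are as effective as the actual ones", and it extends the same benefit to patients with motor disorders.

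**Design and test.** Under Trial design, "All participants will perform both experimental and control conditions". Under Interventions, "The control intervention consists of displaying the same virtual body in 3PP", and the participant sits still in both sessions. Under Primary outcomes, "the main comparison in order to find a significant effect of vHIE on cognitive functions will be 1PP versus 3PP". The Stroop analysis is a repeated-measures ANOVA with TIME (before, after) and CONDITION (1PP, 3PP). The heart-rate analysis also compares 1PP with 3PP. No section describes a session of real exercise, a margin, or a formal comparison with the earlier cycling study.

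**The concern.** The stated goal and conclusions concern virtual versus real exercise. The data concern one virtual display versus another. Rejecting the hypothesis of no difference between perspectives carries no information on how either display compares with real exercise, so the conclusion would not follow even if every prediction came true.

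What is at stake is how a positive result is read. The Discussion looks ahead to sedentary people, people with heart disease and patients with motor disorders. The eligibility criteria require no history of motor disorders, so the trial will hold no data on that last group. A perspective effect in healthy students could be cited as evidence that virtual training matches physical training.

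**Working it through.** **1. What the primary analysis estimates.** Let V1 and V3 be the before-to-after changes in Stroop interference with 1PP and 3PP. In a 2 x 2 within-subject ANOVA, the TIME x CONDITION interaction is a paired test of

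D = V1 − V3.

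The article writes out the same contrast under Correlations.

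**2. What the conclusion needs.** Let R be the change after real exercise. Statements that virtual exercise is the same as, or as effective as, real exercise concern V1 − R, which splits as

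V1 − R = (V1 − V3) + (V3 − R).

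The trial estimates the first bracket. Nothing in it informs the second, because R is never observed. Any value of D is compatible with a virtual effect smaller than, equal to or larger than the real one. The same holds for heart rate and for the fNIRS signal.

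**3. The sample size.** The Sample size section gives 28 participants (30 recruited) for a moderate effect, alpha 0.05 and power 0.8, with no numeric effect size, sidedness or correlation. Under assumed conventional values:

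| Assumed test | n for 80% power |
|---|---|
| Paired t, standardised difference 0.5, one-sided | 27 |
| Paired t, standardised difference 0.5, two-sided | 34 |
| Repeated-measures F, f = 0.25, 2 measurements, correlation 0.6 | 28 |
| Repeated-measures F, f = 0.25, 3 measurements, correlation 0.5 | 28 |

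The t rows use noncentrality 0.5 × √n. The F rows use noncentrality f² × n × m / (1 − ρ), with m measurements and correlation ρ. Some variants give 28, so the figure is not called wrong. Each of them sizes a test of difference, and none sizes an equivalence test.

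**4. The size of D needed for significance.** With n = 30 and a two-sided 0.05 test, the observed D must reach 2.045 / √30 = 0.37 SD of the paired difference. This threshold is set by the sample size and has no link to a real-exercise benchmark.

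**5. Illustration: what an equivalence claim would take.** Suppose real exercise were added as a paired condition. Take two one-sided tests at 0.05 each, power 0.80, a true difference of zero, and margin δ in SDs of the paired difference (normal approximation):

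n = ((1.6449 + 1.2816) / δ)².

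| Assumed margin δ | n for 80% power | Power at n = 30 |
|---|---|---|
| 0.20 | 215 | about 0 |
| 0.25 | 138 | about 0 |
| 0.30 | 96 | about 0 |
| 0.50 | 35 | about 0.73 |

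At n = 30, the smallest margin with 80% power is 2.9264 / √30 = 0.53 SD. The margins are assumptions, because the article gives none. The table shows only that equivalence is a different question from the one the trial is sized for.

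**The case against.** **The governing sections are already narrow.** Primary outcomes gives the main goal as a beneficial effect of 1PP vHIE on executive functions, judged against 3PP. Statistical analysis says the trial is designed to determine whether a virtual intervention is beneficial, and the abstract's discussion is also restrained. This stands, and it is why the point is about wording. But it also means that the Purpose and Discussion go further than the article's own analysis sections.

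**Comparable and same may mean the same kind of effect, not the same size.** That is a possible reading of the Purpose and of the first Discussion statement. It does not rescue the statement that virtual movements are as effective as actual ones.

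**The conclusion is conditional and needs several predictions to hold.** True: it rests on better Stroop performance and higher prefrontal activation after 1PP and not after 3PP, preceded by a check of heart rate and questionnaires. Yet none of these involves real exercise, so meeting all of them still leaves R unknown.

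**Stronger readings that the article does not support.**
- A reader might infer that any difference, however tiny, would trigger the conclusion. An observed difference below about 0.37 SD would not be significant. No fraction of the real-exercise effect can be given either, because the article states no real-exercise effect size.
- A reader might infer that the article says the earlier study's population differs from this one. It says that study used sedentary young adults, but this trial sets no activity criterion, so sedentary students are eligible. The stated difference is cycling versus running, already listed as a limitation.
- A reader might infer that practice effects are overlooked, or that the perspective comparison is invalid. Repetition effects, and a possible effect of 3PP itself, are disclosed. The main comparison is between conditions in randomised order.

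**Conclusion.** The point holds as a mismatch between claim and design. The Purpose and Discussion state comparability with real exercise as goal and conclusion, while the trial can support only a statement about 1PP relative to 3PP. The information it yields on virtual versus real exercise is none: no estimate, no interval and no margin against which to judge one. This follows from the two conditions described and needs no numerical assumption; the equivalence sample sizes are illustrative only. An analysis plan could not repair it, because it cannot supply a condition that no participant undergoes. The 1PP-versus-3PP test, the randomisation and the primary outcome are unaffected.

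**What to change.** 1. In the Purpose, and where the Discussion states the hypothesis and what its confirmation would mean, restate the claim along these lines: *vHIE seen in 1PP changes Stroop interference more than the same vHIE seen in 3PP.* This agrees with the Primary outcomes section.
2. Remove, as conclusions of this trial, the statements that virtual exercise is comparable to, the same as, or as effective as actual exercise. Include the extension to patients with motor disorders.
3. Add to the limitations that there is no real-exercise comparator, and that comparability would need such a condition, a pre-specified margin and a sample size to match.

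The cost is a narrower claim. Conduct, randomisation, outcomes and analysis stay as they are. Trial status puts the end of recruitment at May 2019; the wording can still be corrected in the results report after that.

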### Trial status

Recruitment of participants started in February 2019 and will end in May 2019.

## Data Availability

An anonymized version of the main outcome data will be eventually available after publication of the main results paper if explicitly requested.

## Abbreviations

1PP: First-person perspective
3PP: Third-person perspective
Ch: Channels
DLPFC: Dorsolateral prefrontal cortex
fNIRS: Functional near-infrared spectroscopy
HHb: Deoxygenated hemoglobin
HIE: High-intensity intermittent exercise
HR: Heart rate
IVR: Immersive virtual reality
O2Hb: Oxygenated hemoglobin
PFC: Prefrontal cortex
RCT: Randomized controlled trial
ROI: Region of interest
SoA: Sense of agency
SoBO: Sense of body ownership
TDMS: Two-dimensional mood scale
vHIE: Virtual high-intensity intermittent exercise
VR: Virtual reality
